## **Abstract**

**Background:** Low and middle-income countries (LMICs) hold the majority of disease burden attributed to major depressive disorder (MDD). Despite this, there remains a substantial gap for access to evidence-based treatments for MDD in LMICs like Pakistan. Measurement-based care (MBC) incorporates systematic administration of validated outcome measures to guide treatment decision making and is considered a low-cost approach to optimise better clinical outcomes for individuals with MDD but there is a paucity of evidence on the efficacy of MBC in LMICs.

**Methods:** This protocol highlights a randomized trial which will include Pakistani outpatients with moderate to severe major depression. Participants will be randomised to either MBC (guided by schedule), or standard treatment (guided by clinicians' judgement), and will be prescribed with paroxetine (10–60mg/day) or mirtazapine (7.5–45mg/day) for 24 weeks. Outcomes will be evaluated by raters blind to study protocol and treatment.

**Discussion:** With increasing evidence from high-income settings supporting the effectiveness of MBC for MDD, it is now necessary to explore its feasibility, utility, and efficacy in low-resource settings. The results of the proposed trial could inform the development of a low-cost and scalable approach to efficiently optimise outcomes for individuals with MDD in Pakistan.

**Keywords:** Measurement-based care, Treatment guidelines, Depression, Major depressive disorder, Antidepressant treatment

**Trial registration:** NCT05431374

## Introduction

Major depressive disorder (MDD), a leading cause of disability worldwide, is indicated as one of the two most disabling mental disorders by the Global Burden of Diseases, Injuries, and Risk Factors Study (GBD) 2019 (Vos et al., 2020). The GBD study further highlights an increase in incidents of depression worldwide, from 172 million in 1990 to 25.8 million in 2017, representing a drastic increase of 49.86% (Liu et al., 2020). This sharp increment, coupled with the debilitating physical and mental symptoms of MDD, translates into harrowing global health burden. These high rates of prevalence fare worse for low-income and densely populated countries like Pakistan, with a population of more than 220 million. Various epidemiological studies from Pakistan have reported a prevalence of 20-50% for depression (Ahmed et al., 2016; Gadit & Mugford, 2007; Karmaliani et al., 2009). This prevalence occurs in the context of limited access to mental health care with less than 500 psychiatrists for the entire Pakistani population (Sikander, 2020). The paucity of mental health professionals in Pakistan creates a massive treatment gap, which can only be minimized by standardized and cost-effective interventions that result in higher rates of response and remission.

However, despite several effective pharmacological and psychosocial interventions available globally, only about one-third of depressed patients achieve remission (Xiao et al., 2021). Clinical evidence indicates low remission and high dropout rates due to inadequate dose and/or duration of antidepressant medication treatment (R. C. Kessler et al., 2003; Ormel et al., 2019). Quick changeovers from one antidepressant to another or an unnecessarily prolonged treatment trials result in a practice bias (Rush et al., 2006; Trivedi, Fava, et al., 2006), therefore clinical trials exploring the efficacy of depression care specialists report only a modest remission rate of 15% to 35% (Katon et al., 2010; Trivedi et al., 2004). Subjective outcome assessments also lead to wide variances in symptomology, functionality, side-effect frequency and burden (Biggs et al., 2000). This calls for a need to establish scalable clinical management practices which utilize biopsychosocial assessments, formulate a differential diagnosis, and provide evidence-based treatments for patients with MDD (Hong et al., 2021).

Major treatment guidelines from high-income countries emphasize the importance of 'Measurement-Based Care' (MBC), which utilizes outcomes based on validated clinical instruments to

guide treatment decisions (Aboraya et al., 2018; Gelenberg, 2010; Kennedy et al., 2016). This concept was derived from the stepwise treatment algorithm developed through the Sequenced Treatment Alternatives to Relieve Depression (STAR\*D) trial (Trivedi, 2009; Trivedi, Rush, et al., 2006; Trivedi & Daly, 2007). The large-scale trial funded by the US National Institute of Mental Health examined treatment options in an algorithmic manner with the aim to guide the next steps for treatment of patients with MDD who have an inadequate response to an antidepressant. The trial reported significantly improved outcomes, better-informed treatment decisions and greater remission rates in patients with chronic depression. Similarly, in a study of 120 patients with moderate to severe MDD in China, significantly more patients receiving MBC achieved response (86.9% compared with 62.7%) and remission (73.8% compared with 28.8%) compared to those receiving standard care (Guo et al., 2015). Time to response and remission were significantly shorter with MBC (for response, 5.6 weeks compared with 11.6 weeks, and for remission, 10.2 weeks compared with 19.2 weeks). There was also a significantly larger decrease in Hamilton Depression Rating Scale (HDRS) scores (-17.8 compared to -13.6) in the MBC group. The MBC group had significantly more treatment adjustments (44 compared with 23) and higher antidepressant dosages from week 2 to week 24 (Guo et al., 2015). MBC has also been found to help patients gain insight into their illness course; those who completed self-reports of depressive symptoms expressed that the measures allowed them to quantify their symptoms and gain a better understanding of their experience with depression (Dowrick et al., 2009). The better educated patients are about these measurements, the more they adhere to a treatment plan (Trivedi et al., 2020). MBC may also be a valuable tool for facilitating collaborative care among providers within and across organizations (Katon et al., 2010). Given MBC's potential to improve outcomes, it may be one of the minimal interventions necessary for maximal improvement in clinical outcomes in patients with MDD (R. Kessler & Glasgow, 2011).

While significant evidence for effectiveness of MBC is found in clinical settings from high and middle-income countries, assessments of MBC compared with usual care for the treatment of MDD are yet to be completed in low-resource settings like LMICs. Given the high prevalence of MDD, economic burden and limited resources, countries like Pakistan can benefit immensely from assessment and implementation of MBC to enhance outcomes for patients.

## Methods

The aim of this trial is to determine the efficacy and safety of MBC in patients with MDD in comparison with standard care in Pakistan. In order to reduce the variance found in treatment-as-usual and isolate the impact of MBC, standard care for this trial will limit medication choices to either paroxetine or mirtazapine (as per previously published trials). We hypothesize that, compared to standard care group, the MBC group will have significantly higher rates and shorter times to response and remission, along with lower rates of dropout and side effect burden.

### Study design and setting

This will be a multi-center, with assessors blind to protocol and treatment group, parallel arm, randomized controlled trial (RCT). The study is a direct replication of a study conducted by Guo et al. (2015) in China (Guo et al., 2015).

### Participants

Participants will be recruited from psychiatric units of teaching and non-teaching hospitals and primary care settings such as General Physician (GP) clinics and Basic Health Units (BHUs) in 6 centers: Karachi (population 23 million), Lahore (population 10 million), Rawalpindi (population 3 million), Hyderabad (population 2 million) and Quetta (population 1 million) and Multan (1.8 million). By recruiting participants from across the country, we are confident that the sample will be representative of Pakistani patients with MDD.

#### ***Inclusion Criteria***

Adult outpatients (18-65 years of age), diagnosed with nonpsychotic MDD (established by treating psychiatrists and confirmed by a checklist based on DSM-5 criteria at screening) and with a score of at least 18 on the 17-item Hamilton Depression Rating (HDRS-17) (administered as part of the routine pre assessment questionnaire) will be the inclusion criterion of this study. These individuals should also be able to communicate effectively and give written informed consent and be a resident of the trial catchment area.

### ***Exclusion criteria***

We will exclude individuals who have; lifetime history of drug or alcohol dependence; diagnosis of bipolar, psychotic, obsessive-compulsive, or eating disorders confirmed with DSM-5 criteria, history of a lack of response or intolerance to either of the two protocol antidepressants (paroxetine and mirtazapine), suicide attempts in the current depressive episode, any major medical condition contraindicating the use of the protocol antidepressants, or are currently pregnant or breastfeeding.

### **Sample size**

The sample size of 120 participants for this exploratory trial is based on the study conducted by Guo et al. 2015(Guo et al., 2015).

### **Randomization and masking**

Participants will be randomized in a 1:1 allocation to measurement-based vs. standard-care arm. Randomization will be computer generated and use a random permuted block method with variable block sizes. Given the potential differences in recurrence rates in these groups, the sample will be stratified by site and self-reported sex. We will assess other potential prognostic characteristics (age, duration of illness, number of previous episodes, gender) in our a priori subgroup analyses.

Given the nature of the intervention, it will be impossible to blind clinicians in participating centers or the participants, however this will be an assessor blind trial. The assessors will be trained to use instruments, and will carry out assessments at an arms-length from treating physicians. Before assessments, participants will be asked not to reveal any information about treatment to assessors. In case of unintentional unblinding, we will assign new outcome assessors. Statistical analysis will be partially blind (knowing treatment groups, but not what each group is).

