**Ethics approval and consent to participate**

Participants will be recruited at five local sites in Pakistan. The study has been approved by the National Bioethics Committee of Pakistan. All participants will provide written informed consent using a form approved by the local REB and will be advised of their right to withdraw from the study.

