### 3.2. Statistical Analyses

A treatment-blind statistician will analyze the data after completion of follow-ups for all recruited participants using SPSS for Windows, version 20.0 (IBMCorp., Armonk, N.Y.).

Like the Guo et al. (2015) trial, we will use independent-sample t-tests, Mann-Whitney U tests, and chi-square tests, to compare sociodemographic and clinical characteristics, discontinuation, response and remission rates, and side effects as appropriate. Full intent-to-treat analyses will be carried out to determine all-cause discontinuation. Estimated time from randomization to response and remission will be calculated using Kaplan-Meier survival analyses, and a comparative analysis will be facilitated using the Cox proportional hazards regression model. Analysis of covariance will be used to compare the changes in HDRS scores between the two groups. Additional subgroup analysis might be carried out to understand group-differences due to age, gender, duration of illness, and number of previous episodes. The significance threshold will be  $p < 0.05$  (two-tailed) for all analyses.

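### Randomisation is stratified by site and sex, but no stated analysis names either factor, and baseline HDRS is not named as a covariate; this may cost power

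*Combined protocol and SAP*

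**What the plan says.** Protocol, Randomization and masking: "Participants will be randomized in a 1:1 allocation to measurement-based vs. standard-care arm". The sequence will "use a random permuted block method with variable block sizes", and "the sample will be stratified by site and self-reported sex". The reason given is possible differences in recurrence rates between these groups. The section then calls age, duration of illness, previous episodes and gender other potential prognostic characteristics, which implies that the stratifiers are prognostic too.

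SAP 3.2 and the protocol's Statistical analysis section use nearly the same text:

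- t-tests, Mann-Whitney tests and chi-square tests for response and remission rates, discontinuation and side effects;
- Kaplan-Meier estimates of time to response and time to remission, the two primary outcomes, after which "a comparative analysis will be facilitated using the Cox proportional hazards regression model";
- analysis of covariance for HDRS change, with no covariates listed;
- subgroup analyses, which are optional in this section, by age, gender, duration of illness and previous episodes.

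The threshold is p < 0.05, "two-tailed) for all analyses". Site appears in no analysis. Sex appears only as gender, in the subgroup analyses.

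The number of sites is inconsistent. Participants refers to "Basic Health Units (BHUs) in 6 centers", while the ethics declaration says "Participants will be recruited at five local sites in Pakistan".

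**The concern.** Stratified blocks make the arms more alike on site and sex than simple randomisation would. If those factors predict outcome, the treatment estimate varies less from trial to trial. An analysis that leaves them out still computes its standard error as if that variation were present. The test then tends to reject too rarely under the null, and the power bought by stratifying is not collected.

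Site effects are plausible here. Recruitment spans teaching and non-teaching hospitals, GP clinics and basic health units in several cities. Standard care follows local judgement and resources. Each site has its own two HDRS assessors, so differences between raters are also differences between sites.

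Baseline HDRS is a separate matter. It is measured in everyone and enters the definition of response, so it is a natural covariate. It was not a stratification factor, so leaving it out can lose precision but does not distort the error rate in the same way.

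There is also a pre-specification issue. If the SAP does not list the covariates of a regression model, they can be chosen after the data are seen.

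**Working it through.** **The plan's own figure.** The only figure is the total of 120: "The sample size of 120 participants for this exploratory trial is based on the study" it replicates. No power, effect size, event count or dropout is stated, so there is nothing to reproduce. As context, the replicated trial's response rates in the protocol Introduction (86.9% v 62.7%), at two-sided 5%, would need 100 patients for 80% power, 132 for 90%, or 116 for 80% with continuity correction. With 60 per arm the power for response rates is 87%.

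**Implied hazard ratio for response.** Under proportional hazards, HR = ln(1 − 0.869) / ln(1 − 0.627) = 2.06. Expected events are 60 × (0.869 + 0.627) ≈ 90.

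**Stratum sizes.** Six sites × 2 sexes = 12 cells, and 120/12 = 10 patients per cell. Five sites give 10 cells of 12.

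**Limiting case for a continuous outcome.** If the strata explain a share R² of the variance and are perfectly balanced, the true error of the unadjusted nominal 5% test is 2 × (1 − Φ(1.96/√(1 − R²))). This gives 3.9% at R² = 0.10 and 2.8% at R² = 0.20. Balance is not perfect in cells of about 10 with unstated block sizes, so these figures are limits.

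**Simulation of time to response.**

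- From the documents: N = 120, 1:1, six sites, permuted blocks within site and sex, HDRS at weeks 2, 4, 8, 12 and 24, and a control hazard giving 62.7% response by week 24.
- Assumed: 20 patients per site, 60% of one sex, blocks of 2 or 4, 15% uniform dropout, HR 1.75, and the prognostic strengths below.
- Cox models with Efron ties, 1,500 trials per cell. Monte Carlo SE is about 0.6 points for type I error and 1.3 for power.

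Strengths are listed as SD of the site log hazard / sex log HR / baseline HDRS log HR per SD.

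| Assumed strengths | Unadjusted, type I error | Unadjusted, power | + site, sex | + baseline HDRS | Stratified on 12 cells |
|---|---|---|---|---|---|
| 0 / 0 / 0 | 4.2% | 69% | 71% | 71% | 64% |
| 0.3 / 0.2 / 0.2 | 4.9% | 62% | 66% | 67% | 59% |
| 0.6 / 0.3 / 0.3 | 4.3% | 53% | 64% | 67% | 54% |
| 0.9 / 0.4 / 0.5 | 2.5% | 39% | 57% | 63% | 49% |

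The last four columns are power at HR 1.75. Type I error of the two main-effects models was 4.7% to 6.7%.

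**Second simulation.** With 1,000 trials per scenario, HR 1.75 and baseline HDRS entered per point:

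- site SD 0.5, sex 0.3, HDRS −0.06: power 61% → 71% → 73%;
- site SD 0.3, sex 0.2, HDRS −0.04: power 69% → 74% → 75%.

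The arrows run from unadjusted, to site and sex added, to baseline HDRS added.

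**Third simulation, at the implied HR of 2.06.** With the same two sets of strengths, an HDRS SD of 4.5 assumed and 2,000 trials per cell:

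- stronger set: 80% → 85% → 88%;
- milder set: 86% → 88% → 89%;
- no prognostic effect: 90% → 90% → 90%.

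Unadjusted type I error was 3.8%, 4.2% and 5.0% respectively. The second simulation gave 3.1% for the stronger set.

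**Model size.** With six sites, the main-effects model has 1 (arm) + 5 (site) + 1 (sex) + 1 (baseline HDRS) = 8 parameters. At the replicated trial's rates, that is about 90/8 ≈ 11 events per parameter for response. For remission it is 60 × (0.738 + 0.288) ≈ 62 events, and 62/8 ≈ 8 per parameter. Time to remission was not simulated.

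**The case against.** **The documents do not choose an unadjusted model.** A reader might infer that every planned analysis ignores site and sex. Neither document says so. Cox regression and ANCOVA can both carry covariates, and the text is silent on which. This objection stands: for those two models the fault is under-specification. It does not help the t, Mann-Whitney and chi-square tests, which are two-group comparisons as written. Nor does an optional gender subgroup analysis adjust the main comparison.

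**The consequence is conditional.** A reader might also infer that the primary tests run well below 5%. The documents do not support this. They give no prognostic strengths, and the reason offered for stratifying concerns recurrence, which is not a trial outcome. In most simulated scenarios the unadjusted error was between 4% and 5%. The lower values came with stronger assumed effects: 2.5% at the strongest set, and 3.1% or 3.8% at site SD 0.5. This stands and limits the claim.

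**Part of the gain may not be real.** The adjusted models' type I error reached 6.7%, so some of their extra power may be slight anti-conservatism. Also, an unadjusted hazard ratio nearer to 1 is not an added bias: marginal and conditional hazard ratios are different quantities.

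**Comparability.** The trial is described as a direct replication and as exploratory, and its analysis deliberately follows the replicated trial. That is a good reason to report the unadjusted analyses as well. It is no reason to leave the covariates unstated.

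**Conclusion.** The point holds in conditional form. No stated analysis names the stratification factors, three of the named tests cannot use them, and the Cox and ANCOVA covariates are not specified.

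At HR 1.75, leaving site and sex out of the Cox model costs about nothing if they are not prognostic, about 4 to 5 points under mild effects, and about 10 under moderate effects. The strongest set gave about 17 points, but nothing in the documents shows that effects of that size are likely. At HR 2.06 the loss is 2 to 5 points for the milder and stronger sets. Omitting baseline HDRS costs roughly 0 to 6 points more at HR 1.75, at most about 3 outside the strongest set, without making the test conservative.

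The omission itself is certain. Its size rests on assumed prognostic strengths, hazard ratio, dropout, block sizes and equal sites. Adjusting still looks worthwhile, because with no prognostic effect the adjusted model lost nothing beyond simulation error.

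**What to change.** First reconcile the site count (six centres or five sites), since it defines the strata and the site terms. Then, in SAP 3.2:

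1. Fit the Cox models for time to response and time to remission with arm, site, sex and baseline HDRS as main effects. Do not stratify on all site-by-sex cells: with about 10 patients each, that had less power than the unadjusted model in the two weaker scenarios (64% v 69% and 59% v 62%).
2. Name site, sex and baseline HDRS in the HDRS ANCOVA.
3. Compare response and remission rates by logistic regression with the same covariates, or by a Mantel-Haenszel analysis that accounts for both site and sex.
4. Keep the unadjusted analyses as sensitivity analyses, for comparability with the replicated trial.
5. Record the change as made before unblinding. SAP 3.1 reports in the past tense that no interim analyses were done, which suggests the SAP was written late, so timing needs to be explicit.

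The cost is wording: site and sex are known at randomisation, HDRS is measured at baseline, and the models are standard. There are two downsides. The adjusted Cox model may be slightly anti-conservative at this sample size (simulated type I error about 5% to 6.7%), and having fewer remission events calls for the same caution there. The adjusted hazard ratio is also conditional rather than marginal, and the report should say so.

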### **Study Intervention and Procedure**

After providing informed consent, eligible patients will enter a one-week washout phase to eliminate any effects of psychotropic medications previously taken. After washout week, the patients will be assigned to treatment arms based on randomization schedule, where they will receive either **open-label paroxetine**

(10–50mg/day) or open-label mirtazapine (7.5–45mg/day). All patients will be followed for 24-weeks after randomization. This dosage range is recommended by the US Food and Drug Authority (*Paxil - Highlights of Prescribing Medication*, 2022; *Remeron -Highlights of Prescribing Medication*, 2022). Paroxetine is a commonly prescribed antidepressant, working as a selective serotonin reuptake inhibitor, while Mirtazapine, which works as an alpha-2 antagonist, has a different mechanism of action. Similar to the Guo et. al study (Guo et al., 2015), the decision about the prescription of drug and dosage will be made by the treating psychiatrists/GP. Depending on the duration of prescribed dosage, symptoms and side effects, the psychiatrist/GP will make adjustments. In case of intolerability or inefficacy, one medication change between paroxetine and mirtazapine will be allowed. Short-acting benzodiazepines, prescribed occasionally for agitation, anxiety, and insomnia, will be permitted, as well as any other medications not affecting the CNS.

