### ***Measurement-based Care***

At every outpatient visit, patient’s feedback will be recorded through the 16-item Quick Inventory of Depressive Symptomatology–Self-Report (QIDS-SR) (Rush et al., 2003) and the Frequency, Intensity, and Burden of Side Effects Rating scale (FIBSER) (Wisniewski et al., 2006). The QIDS-SR is used to measure depressive symptoms in the past one week, with higher scores indicating higher severity (Rush et al., 2003). FIBSER is completed by the patient to report antidepressant side effects on the domains of frequency, intensity, and burden (Wisniewski et al., 2006). A total score >4 is indicative of current treatment being unsuitable and requires revision to dosage/medication (Trivedi, 2009).

The patient’s responses on these self-report measures will inform and guide physician’s decisions. Following a stepwise approach, the treatment schedule will outline the dosage adjustment, and medication changes needed to mitigate the side effects, and promote therapeutic benefit for each patient. Originally driven from the STAR\*D project ([www.star-d.org](http://www.star-d.org)), the treatment schedule used by the Guo et. al. (2015) study (Guo et al., 2015) will facilitate the treatment schedule (Table 1), for this study. However, the starting dosage has been modified following a discussion with the stakeholders, which highlighted patient preference for slower dose titration when initiating preference. Treating physicians will undergo a two-day training to get acquainted with use of MBC schedule. Moreover, an independent research coordinator will be designated at each site to compare the physician’s clinical notes against the MBC treatment guidelines to ensure compliance and standardization. In case of any deviation from the MBC schedule, the physician will be notified and asked to make necessary treatment amendments.

*Table 1. The Measurement-Based Care Schedule*

| Time Point and Measure  | Clinical Status  | Treatment Plan                                                         |                                                                       |
|-------------------------|------------------|------------------------------------------------------------------------|-----------------------------------------------------------------------|
|                         |                  | Paroxetine                                                             | Mirtazapine                                                           |

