|                         | SEs intolerable  | Continue current dose and address SEs, or switch to mirtazapine        | Continue current dose and address SEs, or switch to paroxetine        |
| QIDS-SR score, $\geq 9$ | Nonresponse      | Increase to 40 mg/day                                                  | Increase to 45 mg/day or switch to paroxetine                         |
|                         | SEs intolerable  | Switch to mirtazapine                                                  | Switch to paroxetine                                                  |
| Week 8           |                  |                                                                        |                                                                       |
| QIDS-SR score, $\leq 5$ | Remission        | Continue current dose                                                  | Continue current dose                                                 |
| QIDS-SR score, 6–8      | Partial response | Continue current dose or consider increasing to 50 mg/day              | Continue current dose or consider increasing to 45 mg/day             |
|                         | SEs intolerable  | Switch to mirtazapine                                                  | Switch to paroxetine                                                  |
| QIDS-SR score, $\geq 9$ | Nonresponse      | Switch to mirtazapine                                                  | Switch to paroxetine                                                  |
|                         | SEs intolerable  | Switch to mirtazapine                                                  | Switch to paroxetine                                                  |
| Week 10          |                  |                                                                        |                                                                       |
| QIDS-SR score, $\leq 5$ | Remission        | Continue current dose                                                  | Continue current dose                                                 |
| QIDS-SR score, 6–8      | Partial response | Continue current dose or consider increasing to 60 mg/day              | Continue current dose or consider switch to paroxetine                |
|                         | SEs intolerable  | Switch to mirtazapine                                                  | Switch to paroxetine                                                  |

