### ***Control/Standard-care***

Local medical, psychiatric and family medicine services provide routine care according to their clinical judgment and available resources. Standard-care will be ascertained by the participant's treating physician based on the patient's clinical needs. Research staff will record the nature and intensity of standard-care delivered to each participant. In current practice, MDD patients are not routinely referred for any psychological therapies in Pakistan. Standard-care in Pakistan largely comprises of pharmacotherapy.

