## **Assessment Procedure**

This trial will include two experienced treatment-blind assessors at each site, who will independently administer the mentioned outcome measures at baseline and at 2, 4, 8, 12, and 24 weeks. The research coordinator at each site will advise and remind patients at each visit about non-disclosure of their treatment groups to the assessor.

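### The upper paroxetine dose is 50 mg/day in the Methods range but 60 mg/day in the Abstract and in one optional step of Table 1, and the documents do not show which is intended

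*Combined protocol and SAP*

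**What the plan says.** Three places in the protocol bear on the upper paroxetine dose.

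- **Study Intervention and Procedure** (Methods), for patients assigned to either arm, gives the paroxetine and mirtazapine ranges as "10–50mg/day) or open-label mirtazapine (7.5–45mg/day". It then adds: "This dosage range is recommended by the US Food and Drug Authority".
- **Abstract**, Methods paragraph: patients "will be prescribed with paroxetine (10–60mg/day) or mirtazapine (7.5–45mg/day) for 24 weeks".
- **Table 1** (under Measurement-based Care), week 10, QIDS-SR 6–8, paroxetine column: "Continue current dose or consider increasing to 60 mg/day".

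Three further statements affect how the difference plays out.

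- Table 1 is taken from the replicated trial's schedule, and the only change declared is that "the starting dosage has been modified following a discussion with the stakeholders".
- A site coordinator compares the physician's notes with the MBC schedule: "In case of any deviation from the MBC schedule, the physician will be notified and asked to make necessary treatment amendments".
- Control/Standard-care gives no dose range of its own. It says: "Research staff will record the nature and intensity of standard-care delivered to each participant".

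The SAP contains no dose range.

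**The concern.** A dose range in the Methods is something sites prescribe to and monitors check against. Here the treatment schedule permits a dose outside that range, which creates two problems.

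First, the protocol's stated justification, the regulator's recommendation, is attached only to the range ending at 50 mg/day. It does not cover a dose that the protocol's own schedule allows. The MBC compliance check would not catch this, because it compares prescribing with the schedule and not with the Methods range.

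Second, Table 1 applies to the MBC arm only. For standard care, the Methods range is the only one in the body text. Read literally, one arm may go to 60 mg/day and the other stops at 50. The trial restricts medication to two drugs so that the effect of MBC can be isolated, and the protocol's Introduction reports higher antidepressant doses under MBC in the trial being replicated. A ceiling that is not clearly common to both arms makes a difference in dose harder to interpret.

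**Working it through.** No sample-size or power formula applies. The check sets the printed ranges side by side.

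| Place in the protocol | Applies to | Paroxetine upper dose | Mirtazapine upper dose |
|---|---|---|---|
| Abstract | both arms | 60 mg/day | 45 mg/day |
| Study Intervention and Procedure | both arms | 50 mg/day | 45 mg/day |
| Table 1 | MBC arm | 60 mg/day | 45 mg/day |

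**Size of the gap.** 60 − 50 = 10 mg/day, and 10/50 = 20% above the Methods figure. Mirtazapine agrees in all three places, so the discrepancy is confined to paroxetine.

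**Is it a text-extraction fault?** Probably not. The paroxetine steps in Table 1 run 10–20 (week 0), 20 (week 2), 30 (week 4), 40 (week 6), 50 (week 8) and 60 (week 10), which is a regular ladder. The 50 in the Methods range is also intact.

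**How the 60 mg step is reached and left.** It appears in one cell: week 10, QIDS-SR 6–8, patient on paroxetine. It is optional. Nonresponse at week 8 or week 10 leads to a switch of drug, so nonresponders do not reach it. At week 12 a patient in remission continues the current dose, and one in partial response may do so, which means a 60 mg dose can carry into the rest of the 24 weeks.

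**Which assessments it could touch.** The HDRS is scored "at baseline and at 2, 4, 8, 12, and 24 weeks", which gives five post-baseline assessments.

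- Before week 10: weeks 2, 4 and 8, or 3 of 5. A response or remission already recorded at these visits cannot be altered by a week-10 dose change.
- After week 10: weeks 12 and 24, or 2 of 5.

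This shows when an effect could appear. It does not measure the effect: the documents give neither the number of patients who would reach or take the step nor any dose–response information between 50 and 60 mg/day.

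**The case against.** The strongest objection is that this is a drafting slip with little practical weight. The 60 mg figure sits in one optional cell, open only to partial responders on paroxetine at week 10. The protocol does not call either upper figure a maximum, and it leaves choice of drug and dose to the treating psychiatrist or GP. SAP section 3.1 reports in the past tense that no interim analyses were done, which suggests that conduct is well advanced, so correcting the text may change no prescribing. Most of this stands, and it is why the point is minor. It does not remove the contradiction. A stated range normally implies an upper limit, and the three places cannot all be right.

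A reader might also infer more than the documents support.

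- **That the Methods figure is the slip.** Two of the three places say 60, and only the starting dose is declared as changed from the source schedule. But one of the two is an abstract, and the Methods text is the only place that gives a reason for its range. A table carried over from another trial is equally consistent with 50 being deliberate and Table 1 left unreconciled. Settling this needs the label and the earlier schedule, and neither is reproduced.
- **That the arms were treated to different ceilings.** The printed ceiling could differ by arm, but the documents report no doses given.
- **That 60 mg/day is unsafe or outside the label.** The label's content is not in the documents.
- **That the effect on outcomes is small.** The step is late and optional, but nothing in the documents supports an estimate in either direction.

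**Conclusion.** The inconsistency is real and unresolved: the Methods range stops 10 mg/day below the Abstract and Table 1. Which figure was intended, what doses were given, and whether any outcome was affected cannot be determined from the documents.

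Severity is minor. Sample size, significance level, endpoint definitions and the analysis model do not depend on the dose ceiling. The conclusion assumes only that the upper end of a printed range is meant as a limit, and that Study Intervention and Procedure governs standard care because Control/Standard-care gives no range.

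**What to change.** Confirm the intended maximum against the cited label, then state one paroxetine maximum for both arms.

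- **If 60 mg/day is intended:** change the range in Study Intervention and Procedure to 10–60 mg/day, and keep the sentence about the regulator only if the label supports it.
- **If 50 mg/day is intended:** change the Abstract to 10–50 mg/day and delete the 60 mg option at week 10 of Table 1.

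If conduct is complete, also report by arm the number of patients dosed above 50 mg/day. For MBC, the source is the clinical notes already compared with the schedule. For standard care, it is the records kept by research staff. The protocol does not say in terms that those records include dose, so this should be checked first.

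The cost is one number in the Methods, or one number in the Abstract plus one table cell. If conduct is complete, it is also one descriptive row by arm. No test or sample size changes.
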